### Feasibility and preliminary effectiveness design of the EMPOWER-PD

#### Study design and settings

This 12-week pilot for a randomized clinical trial will assess the feasibility and preliminary effectiveness of the EMPOWER-PD and make comparisons with conventional physical therapy (CPh). The EMPOWER-PD intervention protocol was developed according to template for intervention description and replication (TIDieR) checklist [28] (see Additional file 1). The study protocol was described according to the SPIRIT guideline [29] (SPIRIT Checklist see Additional file 2), and its feasibility will be analyzed according to the aspects mentioned in the CONSORT checklist for pilot and feasibility clinical trials [30] (see Fig. 1). The research project was submitted to the University Research Ethical Review Board of the Santa Catarina State University (UDESC), Florianópolis, Santa Catarina, Brazil, according to the terms of Resolution 466/2012, and approved under report n° 2.145.010. The trial was registered on ReBEC–Brazilian Registry of Clinical Trials: Rio de Janeiro (RJ): Scientific Information and Technologic in Health Institute (Brazil); Registry name: A Physiotherapy protocol based on the preferences of the individual with Parkinson Disease for health empowerment, Identifier RBR-7ZBXQ5, Registered 18 August 2017, http://www.ensaiosclinicos.gov.br/rg/RBR-7zbxq5/.

**Fig. 1 Fig1:**
[figure not shown]
EMPOWER-PD feasibility study CONSORT-style flowchart

Participants will be recruited from the BPaRkI of the Center for Health and Exercise Science of Santa Catarina State University–UDESC and written informed consent will be obtained from each participant before the initiation of any treatment. It is important to highlight that at any time; the participant may withdraw from the study without any prejudice. Data collection will be in clinical setting at Catarinense Rehabilitation Center in the city of Florianópolis/Brazil.

#### Sample size

The primary outcome of this pilot for a randomized clinical trial will be the feasibility (adherence, recruitment rates and safety). As in feasibility studies a formal sample size calculation is not required [30], we estimated the number of participants based on qualitative analysis. We will adopt the recruitment of 6–12 participants per group as a recommended for qualitative studies, being adopted the major value (*n* = 12 per group) [31]. Accordingly, we will use the criteria of sampling saturation that means “collecting data until no new information is obtained” [32].

In relation to the quantitative variables, the present study is not intended to be fully powered for detection of statistically significant effects, but it will enable a sample size calculation related to the quantitative variables for a future randomized trial [33]. For that, we plan to select the sample size based on reasonable precision of estimates of standard deviation of quantitative measures which have shown sensitivity in this feasibility study.

#### Randomization

A computerized block randomization procedure will be implemented by a blind researcher. Individuals with PD will be randomly allocated to two arms: (a) EMPOWER-PD or (b) conventional physical therapy (CPh). An independent person will notify the treating physiotherapists by email to ensure concealed allocation. The distribution of the groups will be kept in a closed envelope. The allocation will be on an equal ratio (1:1) between the two groups of interventions, stratifying by sex and by the stages I–III of Hoehn and Yahr scale (HY) [34]. To avoid bias, blinded testers will assess the participants.

#### Participants

##### Inclusion criteria

The inclusion criteria for recruitment will be participants with a diagnosis of Parkinson’s disease confirmed by the neurologist according to the UK PD Brain Bank Diagnostic Criteria [35], classified between the Stages of I to III according to the HY scale and stable medication regimen for at least 4 weeks before the intervention.

##### Exclusion criteria

Subjects with severe cognitive alterations that will impede the comprehension of questionnaires (score ≤ 26 for schooling over 8 years, ≤ 18 for schooling between 4 and 8 years, and ≤ 13 for illiterate participants in the Mini-Mental State Examination (MMSE)) [36], or those with contraindications for the practice of physical exercises will be excluded.

#### Interventions groups

The treatment sessions will be performed in group, twice a week, for 8 weeks, completing 16 sessions followed by a 4-week follow-up period. Before and after each session, blood pressure will be measured. The exercise intensity will be monitored every 5 min by an oximeter and the modified Borg scale [37] will be applied to verify the perception of effort in both groups by two physical educators for group. However, in the CPh group, the exercise intensity will be controlled between 55% and 85% of maximum heart rate (HR_max_) [2], according to the Karvonen’s formula. Each individual value will be calculated previously the interventions and vebaly stimulated during the session by the physical educator to keep up with the recommended HR values, increasing or slow walking speed. It is important to note that the intensity of the EMPOWER-PD protocol will be self-controlled according to the self-perception of effort of each one. The activities will be carried out during the “on” phase of the medication lasting 1 h, divided into 10 min of heating, 40 min of main part, and 10 min of back to calm [38] in an outpatient space.

##### Empower-PD

Before the intervention sessions, the physiotherapist responsible for applying the interventions will collect the preferences of each participant from an anamnesis with questions such as what is your routine on a weekday? and on the weekend?; what activity do you most enjoy doing in your routine?; what do you like to do in your free time?; do you practice any kind of art?; in what daily life activity can you perceive your body more?; and others if therapist judge necessary in their reality. With this information, the therapist can start to plan how to adapt the protocol to the participants, for example with music, materials used in leisure activities, group dynamics, musical instruments, materials used in their routine, among others.

All the participants recruited and enrolled to EMPOWER-PD protocol will be training in a mixed circuit, at the same time, involving walking in solo training in different contexts (crossing obstacles, reaching activities, circumventing obstacles, passing through narrow spaces, dual-functional-task walking) (Fig. 2). In addition, to sit and stand training and the pivot with progressions will be specific to each task. It will be applied from the main part of 40 min duration, being allowed pauses to rest according to the individual’s perception. The main part starts with all participants inside the circuit. Some individuals will be sitting and in the other side, the others will be standing. When the therapist or the participant said to start, all will move together to the next station. Each station will require different tasks that will progress every 2 weeks focused on their activities of daily living and in challenging exercises according to motor control principles. The circuits will include mounted steps, chairs at different heights and benches, cones, red, green and yellow signs, items of preferential use (gardening, musical instruments, cleaning), which are behind the “U” or pivot-floor marking. The interaction with the preferred items will be done when the participants are in the “U” or pivot, during the period that the whole group went to their positions. Detailed descriptions of the interventions and their progressions are presented in Table 1.

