**Method:**

A 12-week pilot for a randomized clinical trial will assess the feasibility and preliminary effectiveness of the EMPOWER-PD and make comparisons with conventional physical therapy (CPh). Both protocols consist of mobility and locomotion training, and aim at improving motor and non-motor symptoms through different approaches. The EMPOWER-PD aims to provide a source of motivation and empowerment of health through the self-knowledge of the individual’s abilities and limitations, in a protocol that addresses individual preferences. The CPh is based only on physiotherapist decisions, not addressing the individual’s preferences or motivation/empowerment. The target recruitment will be 24 PD individuals, between stages I and III of Hoehn and Yahr (HY), who will be recruited from Brazilian Parkinson’s disease Rehabilitation Initiative (BPaRkI) with allocation ratio 1:1. A computerized block randomization procedure will be implemented by a blinded researcher with the participants blinded to group assignment. The sessions will be conducted in a group setting, twice a week, during 60 min for 8 weeks, followed by 4 weeks of follow-up. The primary outcomes will be the feasibility data (adherence, recruitment rate, and safety). The secondary outcomes will assess the preliminary efficacy on qualitative assessment about individual’s motivation/empowerment and quantitative motor outcomes (Timed Up and Go and Dynamic Gait Index) and non-motor symptoms (6-min walk test and Fatigue Severity Scale). The recommendation to have 6–12 participants per group will be adopted based on the qualitative analysis to the sample size.

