One of the peculiarities of the EMPOWER-PD is the possibility to expand the learning with other participants in group. We believe that this is a very special aspect of this protocol because it provides benefits to both activity and participation [27]. As previously mentioned, the EMPOWER-PD comes as a new approach for individuals with PD and for the physiotherapists involved in this process. During the development of this protocol, we also seek to a new way of acting as a therapist. In this case, there could not be space for hierarchy and differences [7, 9, 12], since the re-encounter with health is in all people involved. As knowledge is shared either through professional expertise or through the experience of living with PD, it must be kept in mind that we are all “people” behind the role of therapist and patient and this is also what EMPOWER-PD seeks to put into focus.

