**Fig. 3 Fig3:**
[figure not shown]
Conventional physical therapy protocol

The therapists will have free choice to use feedbacks, and their instructions will be more related to the execution of the exercise than to the stimulus of self-knowledge of the patient. In this way, the warm-ups will have active joint mobilization exercises, increasing the speed of movement progressively according to the therapist’s command to the group. In the “back to calm” stage, breathing exercises will be performed, starting from diaphragmatic exercises to sustained inspiration and inspiration in times with the association of the upper limbs.

The training will follow the same EMPOWER-PD base structure (mixed, varied, and in blocks), featuring walking in solo, sit-and-lift, and pivot training with specific progressions for each stage of the circuit and increasing the level of difficulty of the complete task by increasing the speed from the therapist’s command. All the participants recruited and enrolled to the CPh will be training at the same time as well as in the Empower-PD group. However, we will control the exercise intensity (55 to 85% of HR_max_, as described previously). The therapy will be in group but without doubles or trios. The materials used in this protocol are the same as the EMPOWER-PD with the addition of the timer to control the execution speed of the circuit in some stages of the CPh protocol. The description of the exercises and their progressions during each week are explained in Table 2.

**Table 2 Tab2:** Conventional physical therapy. 8-week physical therapy protocol, twice a week

Weeks/goals	Objective	Exercises	Instructions	Progression
First–second	Increase speed of execution from a comfortable speed to a fast speed.	From sitting, get up and walk in an 8-m track, make the turn to the “U” (1 m), and walk diagonally to sit on the next chair.	Get up from the chair and walk to the “U,” go around it and sit on the next chair. Start by performing at comfortable speed, with each command increasing speed (“a little faster”/“fast”/“as fast as you can without running”).	The “U” will decrease (1 m–80 cm pivot), and the height of the chair (50 cm–45 cm–40 cm). Every three repetitions of the circuit will be given the command to increase the speed.

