### Procedures

The baseline assessment will be conducted once participants have given informed consent. All interviews/scales will be applied individually in a private setting by a blinded researcher, and all participants will receive an identification number. All evaluation will be performed in the afternoon, with individuals on the “on” phase of the medication. Demographics and eligibility criteria information will be collected at the baseline step. From there, the volunteers eligible in the inclusion criteria will be randomized into one of the two groups (EMPOWER-PD group and conventional physical therapy group) by a second researcher not involved in other steps.

Participants allocated to both groups will receive 8 weeks of intervention that will occur at the same time in different places to minimize individuals’ awareness of the differences between interventions. Then, the participants will be assessed at post-intervention, always by the same physiotherapist research, followed by a follow-up period of 4 weeks. The main objective of this stage of the study is to verify if the intervention would be a source of motivation/empowerment of health for a more proactive life, and in this way, decrease the dependency of professional supervision to remain active. For this, the participant will remain 4 weeks without any guidance from the therapist. After this, they will be contacted by phone to schedule the final evaluation, which will be performed on all outcome variables of the others stages of the study. Participants who drop out of the study will also be contacted by phone for the final evaluation.

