### Data management and analysis

For the feasibility analysis, the results will be expressed as percentage and numbers referring to adherence, recruitment rates, and safety, respectively. After qualitative data collection, two authors will perform the total transcription of the audios and notes line-by-line. Then, two authors will start the codification of the *corpus.* After transcription, the corpus will be codified in numbers and their respective groups (e.g., # ID1emp, # ID5cph) by a blinded third researcher, for the later analysis by a fourth researcher. Codes will then be consolidated into categories after an extensive exploration of the material and interpretation of the data obtained according to thematic analysis of the content. From this, entire research team will discuss to formulate inferences.

To verify the preliminary effectiveness regarding quantitative outcomes, the descriptive analysis will be performed with frequency, central tendency, and variability (mean and standard deviation or median and interquartile interval) in the statistical program SPSS 20.0 for Windows (IBM-USA). All results of the preliminary efficacy of the feasibility trial will be described as estimates of 95% confidence interval. An intention-to-treat analysis will be done with participants including who eventually will be missed in any part of the study.

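### Each arm appears to train as one group, so 95% confidence intervals computed as for independent participants would overstate precision, by an amount that depends on an unstated ICC

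*Protocol article*

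**What the plan says.** Participants are randomized individually: "The allocation will be on an equal ratio (1:1) between the two groups of interventions" (Randomization). The abstract's target is 24. The Sample size section starts from "We will adopt the recruitment of 6–12 participants per group as a recommended for qualitative studies" and takes the upper value, 12 per arm.

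Delivery is collective in both arms. In the Empower-PD section, "All the participants recruited and enrolled to EMPOWER-PD protocol will be training in a mixed circuit, at the same time". In the Conventional physical therapy (CPh) section, "All the participants recruited and enrolled to the CPh will be training at the same time as well as in the Empower-PD group". Under Procedures, both arms "will receive 8 weeks of intervention that will occur at the same time in different places".

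Mutual influence is intended in EMPOWER-PD. The development section values "the possibility to expand the learning with other participants in group". The Empower-PD section adds shared preference items, a circuit chosen by the group in the last two weeks, and a group talk closing each session.

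Objective (iii) compares the arms on motor and non-motor outcomes through 95% intervals. Data management and analysis lists simple descriptive statistics and says that "All results of the preliminary efficacy of the feasibility trial will be described as estimates of 95% confidence interval". The Sample size section intends the pilot's standard deviations (SDs) to inform the sample size of a later trial. The article does not mention clustering, a group effect, an ICC or a design effect.

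**The concern.** When everyone in an arm trains together, their outcomes after treatment can share the influence of that group, that place and whoever leads it. With one group per arm, this shared part moves with the arm contrast and is invisible in the scatter within the arm. An interval built only from that scatter then leaves out a source of variation.

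Two uses are affected. The intervals are the only inferential output for objective (iii), where the Background hypothesizes similar effectiveness, and a judgement of similarity leans on interval width. A difference due to one good or bad group could also be read as an effect of the approach. Second, a definitive trial delivered in groups would be too small if it were sized from the pilot SD as though participants were independent.

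**Working it through.** **Inputs from the document.** 12 per arm in two arms; one group per arm, read from the Empower-PD, CPh and Procedures sections; 95% intervals.

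**Assumptions.** The ICC is not given; 0.01, 0.05 and 0.10 are used. The naive interval is taken to be a two-sample t interval with 24 − 2 = 22 df.

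**The plan's own figure.** 2 × 12 = 24, which agrees with the abstract. The plan states no power calculation to reproduce.

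**Standard error.** Set the total variance to 1 and the group size to m = 12.

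- True variance of an arm mean: [1 + (m − 1)ICC]/m. The numerator is the design effect, DE.
- With one group per arm, the within-arm variance estimates only 1 − ICC, so the naive variance of an arm mean is (1 − ICC)/m.
- True SE divided by naive SE: √[DE/(1 − ICC)].

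The coverage of a nominal 95% interval is the probability that a t variable with 22 df lies within ±2.074/ratio. A simulation of 200,000 runs per ICC gave 93.7%, 88.2% and 81.2%.

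| ICC | DE | DE/(1 − ICC) | SE ratio | Coverage | Pilot SD / total SD = √(1 − ICC) |
|---|---|---|---|---|---|
| 0.01 | 1 + 11 × 0.01 = 1.11 | 1.12 | 1.06 | about 94% | 0.995 |
| 0.05 | 1 + 11 × 0.05 = 1.55 | 1.63 | 1.28 | about 88% | 0.975 |
| 0.10 | 1 + 11 × 0.10 = 2.10 | 2.33 | 1.53 | about 81% | 0.949 |

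**If training ran in waves.** With two groups of 6 per arm, DE = 1 + 5 × ICC = 1.05, 1.25 and 1.50. The within-arm variance then captures part of the group variance; its expectation is 1 − 5·ICC/11. The SE ratio is √[(1 + 5·ICC)/(1 − 5·ICC/11)] = 1.03, 1.13 and 1.25. The intervals are still too narrow, but less so.

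**Size of the SD effect.** The post-treatment SD is understated by 0.5%, 2.5% and 5.1%. Baseline SDs come before any group treatment and are unaffected.

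**Consequence for a later trial.** Take for illustration a standardized difference of 0.5, 80% power, two-sided 0.05 and groups of 12. None of these is in the document.

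| ICC | Per arm, pilot SD, no design effect | Per arm, total SD with design effect |
|---|---|---|
| 0.01 | 63 | 70 |
| 0.05 | 60 | 98 |
| 0.10 | 57 | 132 |

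Almost all of the gap comes from the missing design effect. A sample size based on the post-treatment within-group SD has to be multiplied by DE/(1 − ICC), not by DE alone: at ICC 0.10, 57 × 2.10 is about 120, short of 132.

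**The case against.** **The interval method is not written out.** A reader might infer that the plan commits itself to intervals for independent participants and so states wrong error bars. It gives no formula, and an article may leave that to an analysis plan. This stands, so the point is conditional. But no analysis plan can estimate the group variance from one group per arm. It could only add a caveat or an adjustment for an assumed ICC.

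**The ICC is wholly assumed.** This stands. At 0.01 the effect is trivial, and nothing in the document favours the upper end for individually measured tests. The direction of the error also requires a positive ICC and interest in groups beyond those treated. The intended peer influence makes exactly zero hard to defend, but it does not set the size.

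**One group per arm is not certain.** Under Trial status, recruitment runs from August 2017 to March 2018, which leaves room for waves. The text does not mention any. Separate therapists per arm are likewise an inference from concurrent delivery in different places.

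**The SD claim is small.** A reader might infer that the pilot SD is badly understated. It is not: with 22 df, the ordinary 95% limits for a pooled SD run from about −23% to +42%, which swamps a shortfall of at most 5.1% over the assumed range. The document also does not say which time point's SD will be used.

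**The stakes are low.** This stands. Feasibility is primary, the trial is not powered for these outcomes, and the progression criteria under Primary outcomes concern recruitment, retention and adverse events.

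**Conclusion.** The point holds in a conditional form. Each arm appears to train as one concurrent group in its own place, so group, place and probably therapist effects are aliased with arm. If the 95% intervals are computed as for independent participants, they overstate precision for any positive ICC. With one group of 12 per arm, the naive SE is too small by a factor of about 1.06 to 1.53 over an assumed ICC of 0.01 to 0.10, and coverage falls to between about 94% and 81%. Waves would reduce the error without removing it.

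The document does not support the stronger readings that its intervals are shown to be wrong, that the pilot SD is materially biased, or that the feasibility conclusions are threatened. For planning, the omitted design effect matters far more than the SD. This is a cheap improvement of modest importance.

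**What to change.** Keep the design. In Data management and analysis:

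- State that the intervals for the quantitative outcomes are conditional on the groups treated, and that the arm contrast cannot be separated from group, place and therapist effects.
- Beside each such interval for an arm difference after treatment, give a sensitivity interval with the SE inflated over an assumed ICC range. For one group of 12 per arm, the factors are 1.06, 1.28 and 1.53 at ICC 0.01, 0.05 and 0.10.
- If more than one group per arm was run, record each participant's group and account for it in the analysis.

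In Sample size, say that the definitive trial will use an ICC range from external sources and its own planned group size m. A sample size based on the post-treatment within-group pilot SD (one group per arm) is to be multiplied by [1 + (m − 1)ICC]/(1 − ICC).

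The cost is a few sentences and one extra table column. The downside is wider reported intervals.
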